## **7.6 Early termination or suspension of the clinical investigation**

The sponsor is authorised to terminate the study early or to suspend the study because of relevant medical or administrative causes. The criteria and reasons for ending the study are documented in detail. Patients who were still receiving treatment at the time of the termination of the trial will be asked to undergo a final examination as part of post-intervention testing at the next possible opportunity. The results of these tests will be documented in the CRF. Should an investigator have ethical concerns regarding the continuation of the study, these must be communicated to the sponsor immediately.

The sponsor is authorised to end the clinical trial prematurely if

- There is unequivocal evidence of treatment benefit or harm
- The patient recruitment rate cannot be reached,
- Serious, unresolvable problems arise with the quality of the data collected,
- Unforeseeable circumstances arise in the trial site, which means that the continuation of the clinical investigation is not permissible,
- Unexpected unacceptable side effects occur from the RAGT intervention,
- Unreasonable risks arise (decision after another risk/benefit assessment),
- New scientific knowledge acquired during the study no longer permits the continuation of the study (e.g., reports of unsuspected and unacceptable treatment side effects),
- No trends emerge as for the benefit of the RAGT intervention after a reasonable number of patients have been investigated and the results clinically interpreted,
- There is a lack of compliance in a large number of patients,
- Withdrawal of the LEXO® robotic gait trainer from the market

The PI can decide whether to terminate the study in consultation with the sponsor.

Should an investigator have ethical concerns regarding the continuation of the study, these must be communicated to the sponsor immediately.

## **7.7 Medical care after exit from the clinical investigation**

In principle, the intervention of this clinical investigation is part of the clinical rehabilitation routine i.e., the usual treatment of the patients and not an add-on treatment. After patients have terminated their participation in this study, their treatment will be continued according to their treatment scheme in the same way as during the study. This includes their medication and usual physiotherapy or any other medical treatment or assessment.

## **7.8 End and closure of the clinical investigation**

The end of the clinical investigation refers to the point of final data capture i.e., the date of last patient last visit (LPLV). This is followed by the study analyses and drafting a study report. The following end or closure of study notifications and further actions are required:

- End of study notification of the sponsor Tyromotion that the data collection has concluded as defined in the protocol.
- End of study notification of the responsible research ethics committee of by submitting a Declaration of the End of Study Form.
- Provision of the representative of the sponsor with a declaration of the end of study form.
- The end of study declaration and all related correspondence will be retained in the Trial Master File (TMF).
- Closure of study notification of the sponsor that the data analyses have been concluded as defined in the protocol.
- The PI will submit a summary report on the preliminary effectiveness (performance) and safety (adverse events, side-effects, and drop-outs) of the LEXO® robotic gait trainer, but also on usability and feasibility to the sponsor.
- Notification of the sponsor of all (planned) publications resulting from the research.

## **8. STATISTICAL DESIGN AND ANALYSIS**

### **8.1. General aspects of the analysis**

The analysis of this comparative multiple case studies uses mixed methods, integrating quantitative and qualitative data. These data will be analysed together with the intention of gaining an in-depth understanding of the cases. In addition, the use of mixed methods will purposefully be adopted to generate causal propositions. A comparison of the walking, balance, and other outcomes within the cases of one stratum (disease group) and between the cases (disease groups) will be at the heart of the comparative approach.

A single case can also be the source of new insights about critical success factors. For example, it may become apparent that RAGT has improved walking in one patient but failed in others. Therefore, such a case may be selected and the attributes and features that may be responsible for the differences explored in more depth. In addition, triangulation will be used in evaluation to check answers to descriptive questions about the way things are, for example, by confirming semi-structured observations of the intervention with direct measures from LEXO® or standardised subjective observations or motor test performances.

## 8.2. Planned statistical analysis

IBM SPSS Software, release 27.0 (IBM Corporation, Armonk, NY, USA) and GraphPad Prism 9, San Diego, California, will be used for the data analyses. Statistical significance will be defined as a two-tailed p-value  $<0.05$ . The percentage of missing data will be recorded. Using Little's test of missing completely at random (MCAR) (Little, 1988) the data will be checked, signified by a p-value  $>0.05$ .

Descriptive statistics will be used for the baseline demographic variables, primary and secondary endpoints. Continuous data will be checked for normal distribution using the Shapiro Wilk Test, Q-Q plots and histograms. Raw count (absolute and relative frequencies, N (%)) will be presented for count data (N females and males, N falls, most affected body part, and N adverse events if any, adherence (N of training sessions), recruitment, retention and adherence rates) and nominal data (gender)). Medians (range; 25th and 75th percentiles) will be reported for ordinal data (MMSE, NIHSS, EDSS, UPDRS, H&Y, ASIA Scale, SARA, MAS, ONLS, ALSFRS-R, FAC, TCT, FES-I, EQ-5D-5L, BDI-II, FSS, GAS, Smiley Likert Scale), mean (standard deviation (SD)) will be reported for continuous data (age, years of education, disease duration, 10MWT, FGA, 6MWT, TUG, FSST and MFRT).

With respect to the primary endpoint of feasibility, the recruitment rate (%) will be estimated by dividing the number of consenting patients by the N of eligible patients, multiplied by 100. The retention rate determined by dividing the N of patients who completed the study by the N of the total sample, times 100. Adherence rates will be calculated by dividing the N of RAGT sessions (16x) performed by the patients, divided by the N of the scheduled RAGT training sessions over the 4 week study period, times 100 (Osterberg & Blaschke, 2005). The eligibility, recruitment and adherence rates will be calculated with their 95% CI according to the Wilson 'score' method cited by Newcombe (Newcombe, 1998); when the proportion is close to 0 or 1, a Poisson approximation as described by Brown and colleagues will be used (Brown et al., 2001). Furthermore, the number of (serious) adverse events and side effects will be reported.

The first phase of the analysis will involve a descriptive analysis for all disease groups using the mean (SD) or median (range, 25th and 75th percentiles). The second phase of the analysis will include inferential statistics using a pre-post analysis of the data from the total sample (one group). For continuous data, a paired t-test will be performed and for ordinal data, a Wilcoxon Signed Rank test.

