***additional measures for the patients.***

The criteria for feasibility success will be:

- a) a target recruitment rate 3 patients per month.,
- b) a target retention rate of 85%,
- c) a target minimum adherence rate of 75% to the RAGT interventions (12 sessions out of a maximum of 16)

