### 5.3 Sample size

This clinical investigation will be a prospective comparative multiple case study. A comparative multiple case study design with mainly quantitative data but also qualitative data analyses and a cross-case analysis will be used. Mixing methods is a form of triangulation in research seen as mitigating the weaknesses found in single methods (Heale & Forbes, 2013). Triangulation in research is the use of more than one approach to researching a question. The objective is to increase confidence in the findings through the confirmation of a proposition using two or more independent measures (Noble & Heale, 2019). The combination of findings from two or more rigorous approaches provides a more comprehensive picture of the results than either approach could do alone (Noble & Heale, 2019). A multiple case-oriented research strategy will be adopted to acquire knowledge about the outcomes from RAGT within the 8 different patient (disease) groups, learn about similarities and differences between individual cases and neurological disorders within study intervention periods and emerging patterns (Ababacar et al., 2020; Nordbeck, 2013).

The primary outcome of this study will be the feasibility of the methods and of a larger randomised controlled trial. Based on the study design (Yin, 2014) and primary outcome, no formal sample size calculation has been carried out. Based on the different prevalence rates of the diseases investigated in this clinical investigation, 5 patients with severe stroke in the subacute phase will be included in this study, 5 patients with mild to moderate stroke in the chronic stage, 5 patients with MS, 5 patients with PD, 2 patients with spastic para- or tetraplegia caused by any type of spinal cord lesion, 2 patients with mild to medium grade hereditary ataxia, 2 patients with acute or chronic inflammatory demyelinating polyneuropathy (e.g., GBS, CIDP) and 2 patients with motoneuron disease (e.g., ALS), resulting in a total sample size of 28. Based on the study design, methods and objectives, no further patients will be included to account for attrition, which is expected at 10%.

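### The session-level Wilson interval for adherence ignores clustering within patients and overstates precision; retention, which has a target, gets no interval

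*Protocol*

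**What the plan says.** Section 8.2 (Planned statistical analysis), repeated in the synopsis row on statistical analysis, defines the adherence rate this way: "Adherence rates will be calculated by dividing the N of RAGT sessions (16x) performed by the patients, divided by the N of the scheduled" training sessions over the four weeks, times 100. It then assigns intervals: "The eligibility, recruitment and adherence rates will be calculated with their 95% CI according to the Wilson" score method, with the fallback that "when the proportion is close to 0 or 1, a Poisson approximation as described by Brown and colleagues will be used". Sessions nested within patients are not mentioned.

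Retention is defined in the same paragraph: "The retention rate determined by dividing the N of patients who completed the study by the N of the total sample, times 100". It is not among the rates that receive an interval.

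Section 4.8 lists the criteria for feasibility success, which is the primary endpoint. Two of them are "a target retention rate of 85" per cent and "a target minimum adherence rate of 75% to the RAGT interventions (12 sessions out of a maximum of 16"). Section 5.3 fixes the number of patients, "resulting in a total sample size of 28", and expects 10% attrition without replacement. Section 7.1 gives 16 intervention units per patient.

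**The concern.** A Wilson interval is valid for independent yes/no trials. The adherence numerator and denominator count sessions, and sessions belong to patients. Section 7.5 removes a patient from the study for a relapse or other exacerbation, for a medication change that affects walking, or on withdrawal of consent, and each such exit loses every later session at once. The eight strata run from severe subacute stroke to mild chronic stroke, so attendance probably also differs between patients who stay. Both features make sessions within a patient alike, and 448 sessions then carry less information than 448 independent trials. The Poisson fallback makes no allowance for this either.

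At stake is how precisely adherence appears to be known when the follow-up randomised trial is planned. Separately, retention has a numerical target and rests on only 28 patients, yet section 8.2 would report it as a bare percentage.

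**Working it through.** **Inputs.** 28 patients (5+5+5+5+2+2+2+2, section 5.3); 16 sessions each (4 per week x 4 weeks, section 7.1); targets of 75% adherence and 85% retention (section 4.8). The intraclass correlation (ICC) of sessions within a patient is not in the protocol, so a range is assumed.

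**The protocol's own figure.** 12/16 = 75%, as stated. Sessions in total: 28 x 16 = 448.

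**Interval as planned.** Wilson 95% limits are [p + z²/(2n) ± z·√(p(1−p)/n + z²/(4n²))] / (1 + z²/n), with z = 1.96. For p = 0.80 and n = 448 the centre is (0.80 + 0.00429)/1.00857 = 0.7974 and the half-width 0.0370, giving 76.0 to 83.4%.

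**Allowing for clustering.** Design effect = 1 + (16 − 1) x ICC; effective n = 448 / design effect; the same Wilson formula is then applied. Coverage is that of the planned interval in a beta-binomial simulation (28 patients x 16 sessions, true adherence 80%, 40,000 runs).

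| Assumed ICC | Design effect | Effective n | 95% CI at 80% observed | Width relative to planned | Coverage of the nominal 95% interval |
|---|---|---|---|---|---|
| 0.05 | 1.75 | 256 | 74.7–84.4% | 1.3 | 86% |
| 0.1 | 2.5 | 179 | 73.5–85.2% | 1.6 | 78% |
| 0.2 | 4.0 | 112 | 71.7–86.4% | 2.0 | 67% |
| 0.3 | 5.5 | 81 | 70.1–87.2% | 2.3 | 59% |
| 0.5 | 8.5 | 53 | 67.3–88.6% | 2.9 | 49% |

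**An illustration that needs no assumed ICC.** Let 25 patients attend 14 sessions each and 3 drop-outs attend 3 each, which is close to the expected attrition (3/28 = 10.7%). Adherence is (350 + 9)/448 = 80.1%. The planned Wilson interval is 76.2 to 83.6%. A t interval on the 28 per-patient rates (SD 0.217, SE 0.041, t = 2.052 on 27 df) is 71.7 to 88.5%, about 2.3 times as wide (16.8 against 7.4 points).

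**The point estimate does not move.** With 16 sessions scheduled for everyone, Σxᵢ/(28 x 16) equals the mean of xᵢ/16. The pooled rate and the mean per-patient rate are the same number; only the interval differs.

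**Session rate versus patient threshold.** If half the patients attend 16 sessions and half attend 10, session adherence is 13/16 = 81%, yet only 50% of patients reach 12. If 25 attend 13 and 3 attend 2, session adherence is 331/448 = 73.9%, yet 25/28 = 89% reach 12. A target set on one measure cannot be carried over to the other.

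**Retention.** Wilson on n = 28: 24/28 = 85.7%, the smallest count that meets 85% (23/28 = 82.1%), has 68.5 to 94.3%. For 25/28 = 89.3%, about the expected attrition, it is 72.8 to 96.3%.

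**The case against.** The strongest reply is that nothing is decided on these intervals. A reader might infer that the planned lower limit could clear 75% and make adherence look established when it is not. The documents do not support that reading: section 4.8 gives plain targets, section 8.2 treats the primary endpoint descriptively, and no sentence compares a confidence limit with 75% or 85%. This part of the reply stands in full.

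Second, pooling is inferred. The text speaks of rates in the plural and inserts the per-patient count of 16, and section 5.2 describes a log of each patient's sessions. This stands as a caveat, but the formula counts sessions performed by the patients. If one rate per patient were meant, a Wilson interval on one person's 16 sessions would still assume independence and would give no interval for the trial. Only if the rate were the proportion of patients reaching 12 sessions would Wilson on 28 be right, and the formula does not say that.

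Third, the size rests on an ICC with no source in the protocol, and 80% is an example close to the target. Both are true. At an ICC of 0.05 the widening is modest, and at 85% observed the lower limit is still 79.0% at an ICC of 0.1 and 75.7% at 0.3, falling below 75% only at higher values (73.0% at 0.5). The direction of the error does not depend on the example.

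Fourth, anyone can compute a retention interval from the count, and a separate analysis plan might supply it. That makes the retention point small. It remains because section 8.2 lists which rates get an interval and leaves out one that has a target.

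**Conclusion.** The point holds as a matter of stated precision. Under the natural, pooled reading of section 8.2, the Wilson interval for adherence is too narrow whenever sessions within a patient are positively correlated, and drop-out alone ensures some correlation. The understatement of width is about 1.3-fold at an assumed ICC of 0.05, two-fold at 0.2 and nearly three-fold at 0.5; the nominal 95% interval then covers the true rate in roughly 86%, 67% and 49% of repetitions. These sizes depend on the assumed ICC and on 16 sessions being scheduled for each of 28 patients.

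No feasibility verdict changes under the text as written. The missing retention interval is a minor addition to the same paragraph.

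**What to change.** In section 8.2 and the matching synopsis text:

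- Define adherence as the mean over enrolled patients of sessions performed divided by the 16 scheduled, and keep the 75% target on it. Replace the session-level Wilson interval by a patient-level 95% interval on n = 28 (t, patient bootstrap or cluster-robust).
- As supporting description, report the proportion of patients completing at least 12 of 16 sessions with a Wilson interval on n = 28. Do not attach the 75% target to this proportion: that would change what is being measured.
- Add retention to the rates that receive a Wilson interval. Eligibility can stay in the list.

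The cost is a few sentences. The per-patient session log in section 5.2 already supplies the data and the adherence point estimate is unchanged. The downside is that the reported adherence interval becomes wider.

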### Claims on clinical safety: LEXO®

- *Has passed the 60601-1 test, the machinery directive 2006/42/EG and the 60601-1-2 test*
- *Is developed, approved and produced according to the following ISO standards: ISO 13485, IEC 62366; ISO 14971; ISO 10993 and IEC 62304*

An adverse event data base report has been made based on the systematic search within the worldwide most important databases for medical devices. The results cover adverse event reports, product recalls, and complaints for all years available up to present. Identified search terms targeted Tyromotion devices and software as well as equivalent devices named in the clinical evaluation report (CER). No results and no adverse events were reported for any Tyromotion device and its operating software tyroS version 6.1.

No adverse events happened with LEXO® from its market introduction.

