## 4.8 Primary and secondary endpoints

### Primary endpoint

The primary endpoint of this clinical investigation is the **feasibility** of the methods and of a full-scale randomised controlled trial. This will be assessed by the recruitment rate, retention rate and adherence rate, a structured adverse events log, a Smiley Likert Scale asking four predefined questions on the acceptance of the intervention, as well as a semi-structured observation during the RAGT intervention for understanding the intervention context and process.

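### Section 8.2 summarises adverse events as an event count and a percentage with no defined denominator and no interval, so neither a per-patient risk nor its uncertainty can be read from the result

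*Protocol*

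**What the plan says.** Section 4.8 of the Protocol makes adverse events part of the primary endpoint, feasibility: "This will be assessed by the recruitment rate, retention rate and adherence rate, a structured adverse events log", together with an acceptability scale and an observation of the sessions. The success criteria in the same section cover recruitment, retention and adherence. None concerns adverse events.

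Section 8.2 fixes how the components are summarised. It gives a numerator and a denominator for recruitment, retention and adherence, and then assigns intervals: "The eligibility, recruitment and adherence rates will be calculated with their 95% CI", by the Wilson method, with a Poisson approximation near 0 or 1. Retention is not in that list. On safety the paragraph ends: "Furthermore, the number of (serious) adverse events and side effects will be reported". Earlier in 8.2, adverse events also appear among the items to be shown as absolute and relative frequencies, but the base of the relative frequency is not given.

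Section 5.3 sets the size, "resulting in a total sample size of 28", states that "no formal sample size calculation has been carried out", and expects 10% attrition without enlarging the sample. Section 7.8 asks for a summary report to the sponsor that covers preliminary safety, and the Funding section names safety data among the sponsor's main aims.

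**The concern.** There are two separate weaknesses.

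- **Events are not patients.** Ten events in one patient and one event in each of ten patients give the same count. For the planned trial, the useful quantity is the proportion of patients affected. A percentage of an event count has no fixed meaning until its base is named.
- **No precision is attached.** The section gives intervals to three feasibility rates but none to the safety component. In a sample of 28, a low or zero count of serious or device-related events leaves a wide range of true risks open, and nothing in the planned output shows this.

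The base also matters because of who leaves. Section 9.5 grades an incident as serious when training must be stopped and equates that with a drop-out. Section 7.5 treats disease exacerbation as a drop-out in the analysis. If the percentage were taken over completers, the patients with the most important events could be missing from it. At stake is what the safety summary under section 7.8 can say, and what the later randomised trial can take from it.

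**Working it through.** **Inputs.** Sample size and attrition are from section 5.3, the 16 sessions per patient from sections 4.8 and 7.1, and the 95% level and Wilson method from section 8.2.

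**The plan's own figure.** Four groups of 5 and four groups of 2: 4 × 5 + 4 × 2 = 28. This matches section 5.3. The protocol gives no precision figure for safety, so there is none to reproduce.

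**Step 1: the denominator.** Take ten events as an illustration.

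- All in one patient: 1/28 = 3.6% of patients affected.
- One in each of ten patients: 10/28 = 35.7% of patients affected.
- Events over patients: 10/28 = 35.7% in both cases.
- Events over sessions: 28 × 16 = 448 at most, so 10/448 = 2.2% in both cases.

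The same log therefore yields 2.2% or 35.7% depending on an unstated choice. Neither event-based figure separates the two situations.

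**Step 2: uncertainty when no patient has the event.** Upper limit of a two-sided 95% interval for 0 of n patients, with n = 28:

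- Exact (Clopper-Pearson): 1 − 0.025^(1/28) = 12.3%.
- Wilson: 3.84/(28 + 3.84) = 12.1%.
- Poisson: −ln(0.025)/28 = 3.689/28 = 13.2%. The protocol does not print its Poisson formula, so this form is an assumption.

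One-sided 95% bounds are lower: exact 1 − 0.05^(1/28) = 10.1%, and Poisson −ln(0.05)/28 = 2.996/28 = 10.7%.

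**Step 3: effect of attrition.** 28 × 0.90 = 25.2, so about 25 completers. For 0/25 the limits are 1 − 0.025^(1/25) = 13.7% (exact) and 3.84/(25 + 3.84) = 13.3% (Wilson).

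**Step 4: how easily a zero arises.** The probability of no affected patient among 28 at true risk p is (1 − p)^28:

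| True risk per patient | Probability of 0 in 28 |
|---|---|
| 5% | 23.8% |
| 10% | 5.2% |
| 12% | 2.8% |

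A true risk of 5% would go unseen in about one study of this size in four. A risk near 12% is at the edge of what a zero allows.

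**The case against.** The strongest objection is that this is detail for a statistical analysis plan. The choice between patients and events, the safety denominator and the intervals are commonly settled there, and only the protocol was available for this review. Section 8.2 states nothing false about adverse events, and its list of rates with intervals is not said to be complete. That argument carries weight and keeps the point small. It does not remove it, because section 8.2 itself specifies the adverse event summary, defines the bases of the other rates and chooses which of them get intervals. Followed as written, it gives the weaker output.

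Some stronger readings do not stand.

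- A reader might infer that adverse events are reported only as a raw number. They are also in the N (%) list; the fault is the missing base.
- A reader might infer that adverse events alone were left without an interval. Retention, which has an 85% target, lacks one too.
- A reader might infer that a clean record will be presented as proof of safety. No section says so, no success criterion depends on safety, and section 7.8 speaks of preliminary results. The background statement "No adverse events happened with LEXO® from its market introduction" is market history and says nothing about how this study's events will be analysed.
- A reader might expect a clean record for adverse events of every kind. Section 1.3 anticipates fatigue and mild muscle pain, and section 9.2 defines adverse events broadly, so zero is plausible mainly for serious or device-related events.
- A reader might compute limits for groups of 5 or 2. They would be very wide, but no safety inference by disease group is planned.

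It is also true that patient counts could be recovered later, since each event is logged by patient. That shows the fix is cheap; it does not show that the planned summary is adequate.

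**Conclusion.** The point holds at minor severity. Section 8.2 summarises a component of the primary endpoint by an event count and a percentage of undefined base, with no interval. From that output a reader can obtain neither the proportion of patients affected nor its precision.

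The size, for serious or device-related events: none in 28 patients leaves an upper two-sided 95% limit of about 12% (12.1% Wilson, 12.3% exact), or about 10% to 11% with a one-sided bound. These figures assume that all 28 patients start training, that patients are independent, and that one common risk is meaningful across eight mixed disease groups. The last assumption is a simplification, so the limit describes this case mix and not any single diagnosis. No decision rule in the protocol changes; what changes is what the safety report can properly state.

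**What to change.** In section 8.2, next to the event counts, add text to this effect:

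> The number and percentage of patients with at least one adverse event, at least one serious adverse event and at least one treatment-related event will be reported, with all patients who started training as the denominator. Each percentage will have a two-sided 95% confidence interval (Wilson or exact, one method chosen in advance), and the upper limit will be given when no event is seen.

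State that serious refers to the definition in section 9.4, since section 9.5 uses the same word for a severity grade. Add retention to the rates that get a 95% interval. Events per 100 sessions would be a useful optional extra.

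The cost is a few lines of analysis. No new data are needed: sections 4.8 and 9.7 already have each event logged with dates, severity, causality and seriousness. The safety statement will read slightly less favourably, because an upper limit will stand beside any zero.
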